### Recruitment {15}

If participants meet eligibility criteria, they will be randomised to either the cemented group or the uncemented group, with no other factors of influence.

## Assignment of interventions: allocation

### Sequence generation {16a}

A block randomisation process will be used for this study. A central randomisation list will be computer generated by a consultant statistician at a 1:1 ratio. This method will ensure allocation of patients into the two groups with an equal sample size over time.

### Concealment mechanism {16b}

Randomisation envelopes marked with a randomisation number and containing the corresponding group allocation (cemented or uncemented) will be prepared by an independent member of staff at the institution’s research centre. Patients will be assigned to allocation sequentially according to randomisation number.

### Implementation {16c}

On the day of surgery, the study investigators will locate and open a randomisation envelope in sequence. The randomisation number will be used as the patient’s study ID number and noted in the Case Report Form.

## Assignment of interventions: blinding

### Who will be blinded {17a}

This is a single-blinded trial as the investigators (surgeons) and research staff cannot be blinded to the intervention to deliver treatment and monitor intervention delivery. In order to minimise bias, patients will be blinded to their group allocations for the study period. Pre- and post-operative X-rays will be reviewed by a reviewer blinded to the identity of the patient and of the surgeon.

### Procedure for unblinding if needed {17b}

Patients will be unblinded to the intervention at the end of the trial, unless there is a medical reason to do so prior to the end of the study.

## Data collection and management

### Plans for assessment and collection of outcomes {18a}

Source data will be captured via paper forms that will be either mailed out to participants or filled out at clinic visits. Study windows for data collection have been calculated for each timepoint as follows: Pre-Op, within 2 months before surgery, 6–12 weeks (± 2 weeks), 12 months (± 2 months), 24 months (± 3 months), 5 years (± 6 months) and 10 years (± 6 months).

### Plans to promote participant retention and complete follow-up {18b}

Reasonable effort will be made to ensure a complete dataset, including phone calls for missed questions and to participants who fail to respond after 14 days, and at least three attempts to contact participants at study visits. An X-ray appointment will be made, including for participants who have relocated to ensure radiographs are available for study analysis. Attempts will continue to be made to contact participants who did not complete a study visit for each subsequent study visit.

### Data management {19}

Source data will be collected on paper forms and entered into the electronic study database by trained research staff. The paper case report forms will be stored securely at the investigator site. Archiving will be undertaken in accordance with GCP guidelines. Verification of the data from source documents will also be conducted.

### Confidentiality {27}

Only the investigators and data management team involved with this study will have access to the study database. Participant data will be stored on a secure network only accessible via hospital computers. All data files will be password protected. Only deidentified data will be used for analysis, publication or dissemination. All research staff working on this study will first undergo standard privacy training and signed confidentiality agreements with the hospital.

### Plans for collection, laboratory evaluation and storage of biological specimens for genetic or molecular analysis in this trial/future use {33}

Not applicable as there is no planned collection of biological specimens for this study.

## Statistical methods

### Statistical methods for primary and secondary outcomes {20a}

The primary outcome measure is measurement of progressive radiolucencies graded using the Knee Society Roentgenographic Score (KSRS) [26] at 5 years. The proportion of patients in each group scored at 4 or above (indicating possible progression) will be compared for each compartment using Fisher’s exact test. Descriptive statistics of the KSRS will also be presented at the other follow-ups.

The secondary outcome measures are the OKS, IKSS, FJS, EQ-5D-5L, VAS Pain, Patient Satisfaction and Net Promoter Scores. Results will be summarised as mean and standard deviation for continuous variables, or frequencies and percentages for categorical variables. The differences calculated will be both absolute and as change scores (change from baseline) at each timepoint. Longitudinal outcomes will be analysed using linear mixed effects models, with adjustment for repeated measurements and including important baseline surgery and patient demographics (age, gender, BMI, American Society of Anesthesiologists (ASA) score, smoking status) as covariates. Pairwise comparisons will be compared with *t*-tests (normally distributed) or Mann-Whitney (non-parametric). Categorical data will be compared using Fisher’s exact test or chi-squared tests. A *p*-value of <0.05 will be considered significant. Adverse events will be tabulated separately and reviewed for any commonalities. Revision surgery data from the study will be compared to the revision rates reported in the National Joint Registry [6] at 2 years, 5 years and 10 years.

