The Stryker Triathlon Tritanium® implant that will be used in this study involves complex 3D-printing layering of titanium powder on the surface of baseplates and metal-backed patella [12], creating a highly porous three-dimensional interface. The trabecular titanium coating on the proximal surface of the tibial baseplate is extended to part of the pegs and keels to ensure close contact of the bone-implant interface, allowing for minor inconsistencies with bone resection and morphology. The trabecular titanium metal-backed patella is of a monoblock design. The uncemented implants can also be cemented in situ, which provides the surgeon with intraoperative flexibility once bone quality is assessed. Early reports of the femoral and tibial components of this design show good survivorship in both registry data and peer-reviewed publications [6, 13–15]; however, some studies on previous designs of cementless patella components tend to have higher early revision rates, suggesting a lack of initial press-fit and bony ingrowth [16, 17]. The higher coefficient of friction and rapid ingrowth seen with newer highly porous metal designs may alleviate this issue [11, 18]. Randomised data on fully uncemented (tibial, femoral, patella) in comparison to fully cemented TKA is lacking.

Although cemented fixation remains the gold standard [19], a growing proportion of TKA are now implanted cementless [6, 20]. The aim of the Knee-Fix study is to investigate the long-term implant survival and patient outcomes of fully uncemented compared with cemented fixation in TKA. Our study hypothesis was that uncemented TKA would be as clinically reliable and durable as the gold-standard cemented TKA.

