### Outcomes {12}

The main reason for TKA failure is aseptic loosening; therefore, the primary outcome of interest is implant fixation, which will be measured by assessment of postoperative progressive radiolucencies. Standard anterior-posterior (AP) and medio-lateral (ML) X-rays of the study limb will be obtained pre-operatively and post-operatively at 6–12 weeks, and 2, 5 and 10 years post-operatively (Table 1). Radiographic assessment will be performed following the Knee Society Total Knee Arthroplasty Roentgenographic Evaluation and Scoring System [26], which will produce a single score for each component. All radiographs will be measured by one investigator to ensure consistency. The score at the 5-year follow-up will be the primary outcome of interest; however, the scores at other follow-ups will also be measured and presented.

**Table 1 Tab1:** Patient evaluation schedule for Knee-Fix study: an RCT evaluating cemented vs. cementless total knee arthroplasty

	Study period						
	Enrolment	Allocation	Post-allocation				Close-out
Timepoint	***−t***_***1***_ (−2 months)	0	***t***_***1***_ (6–12 weeks)	***t***_***2***_ (12 months)	***t***_***3***_ (24 months)	***t***_***4***_ (5 years)	***t***_***5***_ (10 years)

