### Sample size {14}

The main outcome measure is the incidence of radiolucencies using plain X-rays. To calculate sample size, we used a non-inferiority test; that is, the uncemented-fixation technique is acceptable if it is not worse than the standard cemented TKA technique based on the incidence of radiographic lucencies. Power calculations were based on estimates from a previous RCT, where 11% of cemented TKA and 2% of uncemented TKA were found to have progressive radiolucencies [21]. Using a power of 80%, 95% confidence level and a non-inferiority limit of 9%, 150 patients are needed in each group. An additional 10 patients per group (5%) will be recruited to allow for loss to follow-up, bringing the target to 160 patients per group (total of 320 patients). The estimated loss to follow-up of 5% is lower than other studies, however is based on previous experience of minimal loss to follow-up of our RCT patient cohorts [32]. Every individual in New Zealand accessing health systems is assigned a national unique health identifier, which allows for comprehensive capture of patient contact details, clinical notes and radiographs, including those who have moved to a different area.

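### The trial is sized on one incidence per knee replacement, but the primary analysis is a separate test for each compartment, with nothing linking those tests to that incidence or to the 9% limit

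*Protocol article*

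**What the plan says.** All statements are in the protocol article.

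- **Sample size {14}:** "The main outcome measure is the incidence of radiolucencies using plain X-rays". The planning rates are that "11% of cemented TKA and 2% of uncemented TKA were found to have progressive radiolucencies", and the result is: "Using a power of 80%, 95% confidence level and a non-inferiority limit of 9%, 150 patients are needed in each group". This is one proportion per arm, counted per knee replacement.
- **Outcomes {12}:** the Knee Society radiographic system is used, "which will produce a single score for each component". Each patient therefore has several scores. The 5-year score is primary.
- **Statistical methods {20a}:** the proportion of patients "scored at 4 or above (indicating possible progression) will be compared for each compartment", using Fisher's exact test, with p<0.05 as the general threshold.

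The Outcomes section speaks of components and the Statistical methods section of compartments. The number of compartments is not given. The Background names three components: "Randomised data on fully uncemented (tibial, femoral, patella) in comparison to fully cemented TKA is lacking". The 9% limit appears only in the Sample size section.

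**The concern.** Both sections claim to describe the primary outcome, but they describe different things. One is a single incidence per knee. The other is a set of proportions, one per compartment. The document does not say how the second becomes the first, which compartment decides, or whether the 9% limit applies to each compartment or to the patient.

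Two consequences follow. First, if one compartment looks acceptable and another does not, the conclusion depends on a rule chosen after the data are seen. This is not far-fetched: the Background reports higher early revision with some earlier cementless patellar designs. Second, a modest excess spread over several components can look acceptable in each one while the share of patients with any affected component exceeds the limit used for sizing.

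**Working it through.** **Inputs from the document.** Control rate 11%; limit 9 points; power 80%; confidence level 95%, sidedness not stated; 150 per group before loss to follow-up; 1:1 allocation. Simultaneous bilateral surgery is excluded, so per knee is read as per patient.

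**Assumptions not in the document.** Three compartments (tibial, femoral, patellar); 11% is the rate of an event in any component; equal rates across components; the 9% limit is applied to each compartment. Independence of components is assumed first, then varied.

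**1. The plan's own figure.** For one non-inferiority comparison with 11% in both arms and one-sided alpha 0.05:

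n = (1.645 + 0.842)² × 2 × 0.11 × 0.89 / 0.09² = 6.183 × 0.1958 / 0.0081 = 149.4, so 150 per group.

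This matches exactly. One-sided 0.025 would give 190. The 150 is thus the size for a single comparison of a single proportion.

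**2. Component rate implied by 11% per patient.** 1 − (1 − 0.11)^(1/3) = 0.0381, or 3.8%.

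**3. An excess of 4 points in each component.** The component rate becomes 7.81%. The any-component rate is 1 − (1 − 0.0781)³ = 21.6%, an excess of 10.6 points per patient, beyond the 9-point limit.

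**4. Chance of passing**, as Φ[(0.09 − d)/SE − 1.645] with SE = √{[p₀(1 − p₀) + p₁(1 − p₁)]/150}, where d is the true excess:

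- One compartment: SE = √[(0.0366 + 0.0720)/150] = 0.0269; Φ(0.05/0.0269 − 1.645) = Φ(0.21) = 58%.
- All three: 0.584³ = 20%.
- One patient-level test: SE = √[(0.0979 + 0.1696)/150] = 0.0422; Φ(−0.0165/0.0422 − 1.645) = Φ(−2.04) = 2%.

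**5. Sensitivity to overlap.** Holding 11% per patient and adding 4 points to each component, the patient-level excess is:

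| Overlap between components | Excess per patient |
|---|---|
| None (3 × 4) | 12 points |
| Independent | 10.6 points |
| Latent normal correlation 0.5 (component rate 4.6%) | 8.2 points |
| Latent normal correlation 0.8 (component rate 6.05%) | 6.3 points |
| Complete | 4 points |

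The 4-point example breaches the limit only when overlap is weak. With stronger overlap a larger component excess is needed: at correlation 0.5, 5 points per component is 10.1 points per patient.

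**6. Alternative success rule.** If any one of three independent tests could carry the claim, one-sided error is up to 1 − 0.95³ = 14.3%, or 1 − 0.975³ = 7.3% at one-sided 0.025. This is a different scenario from step 4, not an addition to it.

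**The case against.** The strongest reply has four parts.

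*A rule for several tests belongs in an analysis plan that is not shown.* This stands for the multiplicity rule alone. It does not remove the conflict between two sections of the same document over what the primary endpoint is.

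*The 11% may already be a component-level rate.* It comes from an earlier randomised trial that is not available here, and the protocol says only that it is a percentage of knee replacements. This stands: the illustration depends on the any-component reading. A component rate can also equal the patient rate, if lucencies overlap fully or occur in one component only, so it would be wrong to say that component rates must be lower.

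*The 9% limit per compartment is not in the plan.* This also stands. The analysis section applies no margin at all, which is a separate defect. Each compartment test also still uses a proportion of patients. What is lost is narrower: 9% as a limit on patients with a progressive radiolucency anywhere in the knee.

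*The effect can be exaggerated.* A reader might infer three stronger results that the documents do not support.

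- Joint power of only 51% if all three compartments must pass (0.80³). That needs an 11% rate in every compartment. At 3.8%, power is about 99% per test and 98% for all three.
- A patient-level excess of 22.7 points passing unnoticed. That is the value with every component exactly on a 9-point limit, where all three independent tests would pass with probability 0.05³, about 0.01%.
- Fisher power of 14% per compartment against 44% per patient for an excess of 3 points per component. With three independent tests, at least one would flag with probability 1 − (1 − 0.138)³ = 36%, so the loss is modest.

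**Conclusion.** The point holds as a contradiction within the protocol article: the Sample size section powers one incidence per knee, and the Outcomes and Statistical methods sections analyse several component or compartment results. Nothing connects them, and a mixed result has no defined conclusion. This rests on the text alone.

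The numerical size is illustrative. Under three independent components, an any-component reading of 11%, and the 9% limit used in each compartment, an unacceptable patient-level excess of 10.6 points would pass all compartment tests about one time in five, against about one in fifty for a single patient-level test. Overlap between components reduces this contrast and can remove it. Error of up to 14.3% arises only if any one compartment suffices, which the document neither states nor excludes.

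**What to change.** In Statistical methods {20a}, define one primary endpoint that matches Sample size {14}: a patient with a score of 4 or above in at least one component (femoral, tibial or patellar) at 5 years. Test it once against the 9% limit. Report component-level proportions with confidence intervals as secondary results. Use one term, component or compartment, throughout, and give the number.

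State in Sample size {14} that the 11% is taken to be an any-component rate for this event. If that holds, 150 per group stands. If 11% were instead the rate in each of three independent components, the any-component rate would be 1 − 0.89³ = 29.5%, and the same formula gives 6.183 × 2 × 0.295 × 0.705 / 0.0081, about 318 per group. The assumption therefore needs to be explicit.

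Cost: no new radiographs or scores. It is, however, a formal amendment to the primary analysis, not an edit of wording. It should go to the ethics committee by the route the protocol sets out and be dated before the 5-year data are analysed. Recruitment has closed, so the sample size cannot be raised if the planning assumption proves wrong.

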## Trial design {8}

The Knee-Fix study is a prospective, single-centre, single-blinded, non-inferiority randomised controlled trial. Eligible participants are enrolled into one of two arms: (1) uncemented group: treatment with total knee arthroplasty using a Stryker Triathlon cementless implant with cementless patellar resurfacing, or (2) cemented group: treatment with total knee arthroplasty using a Stryker Triathlon cemented implant with cemented patellar resurfacing.

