### Interventions

#### Explanation for the choice of comparators {6b}

While cemented fixation remains the gold standard for TKA, the optimal mode of fixation is still debatable. Research comparing the outcomes of cementless vs cemented TKA shows contrasting results [21–23]. In recent years, the use of cementless components has been proposed to offer better biological fixation and improved survivorship due to the improved design features [6, 14, 15]. This prospective randomised controlled trial will help discern long-term differences between the two techniques. As uncemented implants can offer some clinical benefits [13], we plan to conduct non-inferiority analyses, that is, use of fully uncemented TKA is considered acceptable if it is not worse than the gold-standard fully cemented TKA.

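### The trial is sized on a 9-point non-inferiority limit, but the only primary test stated is Fisher's exact test of no difference, which does not use that limit

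*Protocol article*

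**What the plan says.** All references are to the Protocol article.

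- **Trial design {8}** calls the study a "prospective, single-centre, single-blinded, non-inferiority randomised controlled trial".
- **Explanation for the choice of comparators {6b}** says "we plan to conduct non-inferiority analyses", but gives no method.
- **Sample size {14}** says "To calculate sample size, we used a non-inferiority test", cites an earlier RCT in which "11% of cemented TKA and 2% of uncemented TKA were found to have progressive radiolucencies", and concludes: "Using a power of 80%, 95% confidence level and a non-inferiority limit of 9%, 150 patients are needed in each group".
- **Statistical methods for primary and secondary outcomes {20a}** defines the primary outcome at 5 years as the proportion with a Knee Society Roentgenographic Score of 4 or above. These proportions "will be compared for each compartment using Fisher’s exact test". A p-value below 0.05 "will be considered significant".
- **Section {20c}** on non-adherence and missing data adds intention-to-treat and per-protocol analyses, but no test against the limit.

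The 9% limit appears only in the sample size section. No section states a confidence bound, a shifted null hypothesis or a rule for concluding non-inferiority.

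**The concern.** A non-inferiority question asks whether the uncemented arm could be worse by 9 points or more. Fisher's exact test asks whether the data are incompatible with no difference at all. A non-significant Fisher result may mean that the arms are close, or only that the data are too few to tell. It does not rule out a 9-point excess of progressive radiolucencies.

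The design and the stated primary analysis therefore do not match. This is more than detail left to an analysis plan, because the protocol names the primary test. An analysis plan that followed {20a} would inherit the mismatch, and one that departed from it would contradict the published protocol.

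At stake is the trial's main conclusion on durability. With p<0.05 as the only criterion, a non-significant result leaves the reader without a rule. The easiest reading, that the two techniques are equivalent, is also the one with the highest error rate.

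**Working it through.** **Inputs.** From {14}: cemented rate 11%, limit 9% (read as absolute percentage points), power 80%, confidence level 95%, 150 per group (160 with the allowance for loss to follow-up). From {20a}: Fisher's exact test at p<0.05. The protocol does not state sidedness, so Fisher's test is taken as two-sided. The 11% rate is assumed to apply to the endpoint that {20a} analyses.

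**Step 1: reproduce 150 per group.** For a harmful outcome, with pc and pt the cemented and uncemented rates,

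n = [pc(1−pc) + pt(1−pt)] × (z_α + z_power)² / [margin − (pt − pc)]²

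With 11% in both arms, margin 0.09, one-sided α 0.05 (z = 1.645) and 80% power (z = 0.842):

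n = (2 × 0.11 × 0.89) × (1.645 + 0.842)² / 0.09² = 0.1958 × 6.183 / 0.0081 = 149.4, so 150.

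This matches. Other readings at 80% power do not:

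| Basis | n per group |
|---|---|
| Non-inferiority, 11%/11%, one-sided 0.05 | 150 |
| Non-inferiority, 11%/11%, one-sided 0.025 | 190 |
| Non-inferiority, 11%/2%, one-sided 0.05 | 23 |
| Two-sided difference test, 11% vs 2% | 117 (138 with continuity correction) |

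So the limit was used in sizing, with equal rates of 11% and a one-sided 5% level.

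**Step 2: uncemented worse by the full limit.** True rates are 11% cemented and 20% uncemented, 150 per arm. Summing the binomial probabilities over all possible tables gives:

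- Fisher's p is 0.05 or above: 48.1% (44.8% at 160 per arm).
- One-sided 95% Wald upper bound below 9 points: 5.3%.

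48.1 / 5.3 is about 9, so the error rate under the misreading is about nine times that of a test of the limit.

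**Step 3: equal true rates of 11%, 150 per arm.**

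- Fisher's p is 0.05 or above: 96.6%.
- Non-significant, and the one-sided 95% upper bound is 9 points or more: 18%.
- Non-significant, and the two-sided 95% upper limit is 9 points or more: 28% (Wald; 29% with Newcombe).

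**Step 4: a single dataset.** Take 16/150 (10.7%) cemented and 28/150 (18.7%) uncemented. Fisher's p is 0.072. The difference is 8.0 points, with standard error √[(0.1067 × 0.8933 + 0.1867 × 0.8133)/150] = 0.0406. The one-sided 95% upper bound is 8.0 + 1.645 × 4.06 = 14.7 points. The two-sided Newcombe 95% interval is −0.1 to 16.0 points. The result is non-significant, yet non-inferiority is clearly not shown.

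**Step 5: the rates cited in {14}, 11% cemented and 2% uncemented, 150 per arm.** Fisher's test significantly favours uncemented in 87.5% of trials, and in those the upper bound lies below 9 points.

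**Step 6: power of a test of the limit at 11%/11%.** Power = Φ(0.09/SE − z_α), with SE = √(0.1958/n).

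| Rule | 150 per group | 160 per group |
|---|---|---|
| One-sided 95% bound | 80.1% | 82.3% |
| Two-sided 95% interval | 70.2% | 73.0% |

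**The case against.** Four points can fairly be made for the plan.

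1. **Non-inferiority analyses are announced.** Section {6b} does so, and it cannot be said that the investigators never intend to test the limit. This stands. What remains is that the announcement has no method or decision rule, and the one primary test that is named does not use the limit.

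2. **Nothing says that p≥0.05 will be taken as non-inferiority.** This also stands. A reader might infer that a non-significant result will pass as not worse, because p<0.05 is the only criterion given. The document does not say so, and the 48% is a false-claim rate only under that reading.

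3. **The trial could still answer its question in one direction.** A reader might infer that the trial as written cannot answer it at all. That goes too far. A significant Fisher result in favour of uncemented fixation would place it well inside the limit, and under the rates cited in {14} that happens 87.5% of the time (step 5). The gap opens when the arms are similar or uncemented is worse. Equal rates are the case that reproduces the sample size.

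4. **The confidence level is open, and the cost depends on it.** Section {14} says 95% without sidedness. Only the one-sided 95% bound keeps about 80% power at 150 per group. The fix must therefore name the level.

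A further point stands: {20a} compares each compartment separately, while {14} speaks of one incidence. A test of the limit needs to say which proportion it applies to.

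**Conclusion.** The stated primary analysis is wrong for the stated design. The protocol sets and sizes a non-inferiority trial, then names as its only primary comparison a test that ignores the limit, with no rule for concluding non-inferiority.

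The size depends on how a non-significant result is used. If it were read as equally durable, an arm at the unacceptable limit would pass about half the time instead of about one time in twenty. With truly equal rates, about one trial in five or six (18%) would be non-significant without excluding 9 points on the one-sided bound.

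These figures assume an absolute limit of 9 points (supported by the exact reproduction of 150), 150 evaluable patients per arm, a two-sided Fisher test, and an 11% cemented rate for the endpoint analysed. Recruitment was closed in March 2020 and the number achieved is not given, so the actual figures may differ. The mismatch itself does not depend on any of these assumptions.

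**What to change.** In the statistical methods section {20a}:

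- Make the primary analysis the 5-year risk difference, uncemented minus cemented, in the proportion scored 4 or above.
- Declare non-inferiority only if the upper one-sided 95% confidence bound (the upper limit of a 90% interval) is below 9 percentage points. Report this in both the intention-to-treat and per-protocol sets already planned.
- State whether the limit applies to one patient-level proportion (any component) or must be met in every compartment.
- Keep Fisher's test only as a follow-on test of superiority once non-inferiority is shown.
- State that p≥0.05 is not evidence of non-inferiority.

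The change is to analysis wording only, with no new patients or data, and should be fixed before the 5-year outcomes are compared by arm. The price is that the claim becomes harder to make than by a non-significant p-value. If the sponsor prefers a two-sided 95% interval, the stated power must be restated as about 70% at 150 per group; 80% would need 190 per group.
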